### 2.10. Data Management

All researchers will receive formal training regarding the data collection and management. The data will be recorded into computer by two independent researchers. If any differences are noted, corrections will be made based on the original records in CRFs. All paper documents will be saved in a locked filing cabinet, while electronic documents will be stored in a password-protected computer which will be accessible only to the principal investigators.

### 2.11. Sample Size

This pilot study is to evaluate the effect of He's* Santong* needling method on dysphagia after stroke. However, no previous study was found on the effect of acupuncture on the PAS with FEES. A sample size of 30 per group was regarded as a reasonable minimum recommendation for a pilot study [36]. Therefore, we plan to recruit 60 participants.

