## 2. Methods

### 2.1. Study Design

A prospective randomized controlled pilot trial is designed to evaluate the effect of He's* Santong* needling method on dysphagia after stroke. Sixty participants with dysphagia after stroke will be randomly assigned to the treatment group (He's* Santong *needling and swallowing rehabilitation training) and control group (swallowing rehabilitation training) at a 1:1 ratio. The schedule of enrolment, interventions, and assessments is summarized in Table 1, and the flow diagram of the study procedure is presented in Figure 1.

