### 2.12. Statistical Analysis

Statistical analysis will be performed by statisticians that are blind to allocation of group and intervention process. SPSS 22.0 software (International Business Machines Corporation) will be used for statistical analysis. The intention-to-treat population will be the main set for all efficacy analysis. This population will consist of all randomly allocate participants regardless of the type of treatment received. The per-protocol set will be utilized for sensitivity and consistency analysis to compare the results from the intention-to-treat set. All statistical tests will be two-sided, and p<0.05 is considered statistically significant.

One sample of the Kolmogorov-Smirnov test will be used to test the normal distribution of continuous variables. Continuous variables will be shown as means± Standard deviations (SDs) if they are normally distributed or as medians with IQRs if they are not normally distributed. If the measurement data have normal distribution, independent two-sample* t*-tests will be used for comparisons among the groups, while paired* t*-tests will be used for within-group comparisons. If the measurement data are not normally distributed, the Mann–Whitney* U* test will be used for comparisons among the groups, while Wilcoxon signed-ranks test will be used for within-group comparisons.

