## 3. Discussion

Evidence accumulating from clinical trials has indicated that acupuncture is effective for dysphagia after stroke [14]. In clinical practice, combined acupuncture technique has been widely used to enhance the acupuncture effect. However, the combined acupuncture technique studies are still lacking. Therefore, we design this pilot study to evaluate the effectiveness of He's* Santong* needling method for dysphagia after stroke. The advantages of the trial design are shown in the following two aspects.

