### 3.1. Comprehensive Outcome Measures

Instrumental evaluation of dysphagia mainly includes videofluoroscopy swallowing study (VFSS) and FEES. Considering the feasibility, the PAS with FEES is to be selected as the primary outcome. Combined with PAS, FEES is demonstrated as having a high level of agreement with VFSS [31]. Furthermore, VFSS cannot be used at the bedside frequently for follow-up tests because of the necessary exposure to radiation [37]. Compared with VFSS, the FEES is a more appropriate assessment tool for dysphagia assessment after stroke, especially for our study which concerns oral and pharyngeal phase of swallowing [38, 39]. For stroke patients, a bedside test will ensure patient's comfort and compliance.

Saitoh's classification of dysphagia, SWAL-QOL, MMASA, and sEMG will be used as secondary outcome. Saitoh's classification of dysphagia is an ordinary tool to assess the swallowing function of a patient, which has been utilized to evaluate swallowing function in dysphagia patients [32]. SWAL-QOL is a valid, effective, and sensitive tool to assess quality of life of people with dysphagia, which has been used in many studies involved dysphagia management [33]. The MMASA is a useful screening tool for evaluating eating and swallowing functions, which showed relatively high sensitivity and specificity for detecting aspiration [34]. The sEMG is a noninvasive assessment to monitor electromyographic signal of submental muscles, so it is a safe and repeatable method for stroke patients to evaluate strength of swallowing muscles [35].

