### 3.2. Combined Acupuncture Technique

It has been demonstrated that ordinary acupuncture is an effective and safe treatment for dysphagia after stroke [40]. Compared with ordinary acupuncture, He's* Santong* needling method (*Weitong* (normal needling),* Wentong* (fire needling), and* Qiangtong* (bloodletting)) is a combined acupuncture technique, which is often applied to complications after stroke. For effective aspect, He's* Santong* needling method has the potential to increase therapeutic efficacy for dysphagia after stroke, since it combines three monotherapies. For safety aspect, fire needling and bloodletting have been widely used in China for thousands of years [23]. A set of national standard* standardised manipulations of acupuncture and moxibustion* has been established to ensure the safety of acupuncture techniques including bloodletting and fire needling (GB/T 21709.12-2009 and GB/T 21709.4-2008) [28].

It should be noted that our study has certain methodological limitation. Blinding is a crucial measure to assure the quality of the trial. As a limitation, it is difficult to implement blinding in participants because we will adopt a special acupuncture method. In order to overcome this problem, we will minimize the interaction between the participants and acupuncturists. In addition, all outcome assessors and statisticians will be kept blind throughout the whole process.

To our knowledge, this trial is the first attempt to investigate the efficacy of He's* Santong* needling method on dysphagia after stroke. The results of this trial may develop the clinical treatment of dysphagia. However, the biological mechanism of this therapy requires further investigation.

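### The trial is sized only by a pilot rule of thumb, yet it aims at effectiveness through tests at p<0.05; with 30 per group, significant and non-significant results can both mislead

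*Protocol article*

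**What the plan says.** **Size.** The protocol article, 2.11, explains that "no previous study was found on the effect of acupuncture on the PAS with FEES" and then relies on a cited pilot recommendation: "A sample size of 30 per group was regarded as a reasonable minimum recommendation for a pilot study". It concludes: "Therefore, we plan to recruit 60 participants". Section 2.1 sets 1:1 allocation. No effect size, SD, power or allowance for dropout is given.

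**Aim.** Section 2.11 describes the pilot as evaluating the effect of the method. Section 3 says: "we design this pilot study to evaluate the effectiveness of" the needling method. Section 3.2 speaks of investigating efficacy and adds: "The results of this trial may develop the clinical treatment of dysphagia". The article states no feasibility objective, no progression criterion and no plan to use the data to size a later trial. The limitations paragraph in 3.2 names only blinding.

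**Analysis.** Section 2.12 makes the intention-to-treat population the main set for efficacy and states: "All statistical tests will be two-sided, and p<0.05 is considered statistically significant". Between groups it names the t-test or Mann–Whitney U test; within groups, the paired t-test or Wilcoxon signed-rank test. Summaries are to be means with SDs, or medians with IQRs.

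**Outcomes.** There is one primary ("the PAS with FEES is to be selected as the primary outcome", section 3.1). The four secondaries are Saitoh's classification, SWAL-QOL, MMASA and sEMG. All five are measured at Week 0 and Week 4.

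**The concern.** The basis for the size and the use planned for the result do not match. A pilot minimum is chosen because nothing is known about PAS in this setting. The natural product of such a trial is an estimate of the difference, with its uncertainty, to decide on and size a later trial. The article instead states an effectiveness aim and answers it with significance tests.

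Three things are at stake:

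- A non-significant PAS result may be taken as absence of effect when the trial could not exclude a moderate benefit.
- A significant PAS result may be taken at face value although, at this size, estimates that reach significance tend to be too large.
- A single significant secondary outcome, or a significant change within the needling arm, may be taken as efficacy. Section 1 itself says that most patients recover from dysphagia spontaneously, so a within-arm change can be significant with no treatment effect.

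**Working it through.** **Inputs from the article.** 30 per group (2.11); 1:1 allocation (2.1); two-sided 0.05 for every test (2.12); one primary and four secondary outcomes (2.8, 3.1).

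**Assumed, because the article gives none.** Standardised differences d of 0.3 to 0.8 SD; loss of 0%, 10% or 20% (30, 27 or 24 evaluable per group); a two-sample t-test on roughly normal data.

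**1. The article's own figure.** 2 × 30 = 60. This reproduces, but it is the only arithmetic available. There is no power calculation to check.

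**2. Power at 30 per group.** Power = P(|T| > t(0.975, 58)), where T is noncentral t with 58 degrees of freedom and noncentrality d × √(30/2).

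| Assumed d | Noncentrality | Power |
|---|---|---|
| 0.3 | 1.16 | 20.8% |
| 0.5 | 1.94 | 47.8% |
| 0.8 | 3.10 | 86.1% |

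**3. Difference detectable with 80% power.** The normal approximation gives (1.960 + 0.842) × √(2/30) = 0.72 SD. Solving the noncentral t gives 0.736 SD. With 27 or 24 evaluable per group it rises to 0.777 or 0.826 SD. For comparison, 80% power at 0.5 SD needs 63 per group (normal approximation), or 126 in all.

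**4. Precision.** The 95% interval half-width for an unadjusted difference is t(0.975, 58) × √(2/30) = 2.002 × 0.2582 = 0.517 SD. With 27 per group it is 0.546 SD. An observed difference of zero would leave an interval of about −0.52 to +0.52 SD, which still contains a benefit of 0.5 SD.

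**5. Exaggeration.** The same 0.517 SD is the smallest observed difference that reaches p<0.05. If the true effect is 0.5 SD, every significant estimate in the right direction must therefore exceed the truth. By simulation (normal approximation), significant estimates overstate a true 0.5 SD by about 1.4 times on average, and a true 0.3 SD by about 2.2 times.

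**6. Secondary outcomes.** The chance of at least one p<0.05 among four true nulls is 1 − 0.95⁴ = 18.5% if they are independent. Simulated with common correlations of 0.3, 0.5 and 0.7, it is 17.4%, 15.5% and 13.1%. So 18.5% serves as the upper figure.

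**7. Within-group tests.** 5 outcomes × 2 groups = 10 further tests at the same threshold. None of them compares the treatments.

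**The case against.** The other side has a good case, and several stronger readings fail.

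- **The sample size is an error.** A reader might infer this, but 2.11 says openly that no PAS data exist and cites a pilot recommendation. Sizing a pilot this way is legitimate.
- **The outcomes have no hierarchy, so the false-positive risk is 1 − 0.95⁵ = 22.6%.** The article names PAS as the single primary outcome, whose type I error stays at 5%. No rule lets any one of the five count as success, so the pooled figure does not apply.
- **Nothing in the plan yields the variability needed for a later trial.** Section 2.12 reports SDs or IQRs, and PAS is measured at both time points.
- **The trial claims to be confirmatory, and its results will mislead.** It is called a pilot throughout, and the remark on developing clinical treatment is hedged. No passage says how a non-significant or secondary result will be read. At a true 0.8 SD, power is 86%. The results can mislead; it is not certain that they will.

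Two further points stand as limits. Confidence intervals, exploratory labels and multiplicity rules are often left to an analysis plan, which is not shown here, so their absence alone is no finding. And PAS has eight ordered levels and may go to the Mann–Whitney test under 2.12, so the SD-based figures are approximate.

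None of this answers the mismatch itself. The aim, the basis for the size and the significance rule are all stated in the article, and they do not fit together.

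**Conclusion.** The point holds as a mismatch of purpose, size and stated analysis. With 30 per group, the effectiveness question can be answered by p<0.05 with 80% power only if the true difference is about 0.74 SD or more; at 0.5 SD the chance of significance is slightly under one half. A null PAS result leaves a moderate benefit open, and a significant one can be inflated. The risk of up to 18.5% over the secondary outcomes matters only if any one of them is read as efficacy, a reading the article does not rule out.

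The article gives no effect size, SD or dropout rate, so the effect sizes and losses are assumptions. The figures in SD units are indicative for PAS. The plan should be changed, but the change is to wording and emphasis, not to the design.

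**What to change.** - **2.12:** Make the main result the between-group difference in Week 4 PAS, adjusted for baseline PAS, with a 95% confidence interval. Show the distribution of PAS levels by group. Treat secondary and within-group p-values as exploratory.
- **2.11:** Keep 60, and state what it delivers: an unadjusted 95% interval half-width of about 0.52 SD and 80% power only from about 0.74 SD, both approximate for an ordinal scale. Baseline adjustment multiplies the half-width by about √(1 − r²), where r is the correlation between baseline and Week 4 PAS. The article gives no r; assumed values of 0.3 to 0.7 give about 0.49 to 0.37 SD.
- **Discussion (3 and 3.2):** Replace the effectiveness and efficacy wording with a preliminary estimate for deciding on and sizing a definitive trial. Add limited precision to the stated limitations.

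**Cost.** Edits to three places, with no added participants or assessments. The real price is that the trial can no longer claim efficacy from p<0.05.

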### 2.12. Statistical Analysis

Statistical analysis will be performed by statisticians that are blind to allocation of group and intervention process. SPSS 22.0 software (International Business Machines Corporation) will be used for statistical analysis. The intention-to-treat population will be the main set for all efficacy analysis. This population will consist of all randomly allocate participants regardless of the type of treatment received. The per-protocol set will be utilized for sensitivity and consistency analysis to compare the results from the intention-to-treat set. All statistical tests will be two-sided, and p<0.05 is considered statistically significant.

One sample of the Kolmogorov-Smirnov test will be used to test the normal distribution of continuous variables. Continuous variables will be shown as means± Standard deviations (SDs) if they are normally distributed or as medians with IQRs if they are not normally distributed. If the measurement data have normal distribution, independent two-sample* t*-tests will be used for comparisons among the groups, while paired* t*-tests will be used for within-group comparisons. If the measurement data are not normally distributed, the Mann–Whitney* U* test will be used for comparisons among the groups, while Wilcoxon signed-ranks test will be used for within-group comparisons.

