### 2.8. Outcome Measurement

#### 2.8.1. Primary Outcome

*Penetration-Aspiration Scale (PAS) with Fiberoptic Endoscopic Examination of Swallowing (FEES)*. Participants will receive the Fiberoptic Endoscopic examination of Swallowing (FEES) through the fiberoptic endoscopy. They are requested to swallow stained solid food (1 × 1 × 0.5 cm), semi-liquid food (5 ml), and flow food (5 ml and 10ml) in order. If aspiration occurs, the assessment will be terminated. Aspiration will be defined as the entry of stained food into the airway below the levels of the true vocal cords. Silent aspiration will be defined as aspiration occurring in the absence of cough or gag reflex [29]. PAS is an 8-point scale to quantify penetration and aspiration severity that ranges over four stages of oral intake: level 1 (no laryngeal penetration), levels 2~5 (laryngeal penetration), levels 6~7 (tracheal aspiration), and level 8 (silent aspiration) [30]. The combination of FEES and the PAS has been shown to provide reliable and valid assessments [31]. Two experienced clinician assessors will provide a PAS score independently. If they are in disagreement, the expert assessor will confirm a PAS score via consensus.

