#### 2.8.2. Secondary Outcomes

*Saitoh's Classification of Dysphagia*. Saitoh's classification divides the swallowing function into 7 levels: (1) saliva aspirator, (2) food aspirator, (3) water aspirator, (4) chance aspirator, (5) oral problems, (6) minimal problems, and (7) normal. A lower score means more severe swallowing disorder [32].

*Swallowing-Related Quality of Life (SWAL-QOL)*. The scale consists of 44 entries, including appetite, food choice, eating time, symptom frequency, psychological burden, fear, language communication, mental health, fatigue, sleep, and social interaction, summaries all aspects of the quality of life of patients with dysphagia. Each entry has 5 different levels ranging from 1 to 5; a lower score represents more severe dysphagia [33].

*The Modified Mann Assessment of Swallowing Ability (MMASA)*. MMASA is a 100-point scale screening tool for identifying eating and swallowing disorders, which includes 12 items from the Mann Assessment of Swallowing Ability (MASA). The 12 items of the MMASA were alertness, cooperation, respiration, expressive dysphasia, auditory comprehension, dysarthria, saliva, tongue movement, tongue strength, gag, voluntary cough, and palate movements. A lower score means more severe swallowing disorder [34].

*Surface Electromyography (sEMG)*. Activity of submental muscles will be evaluated through sEMG, using a Flexcomp Biomonitoring System. sEMG activity will be detected in the anterior belly of the digastric with a pair of electrodes. Participants will adopt a sitting upright position during the sEMG recording. Two electrodes will be placed on the anterior belly of the digastric muscle parallel to longitudinal axis of the muscle, with the reference electrode placed 3 cm apart from the recording electrode. The peak maximum amplitude will be recorded during 2 ml water swallowing. The recordings will be repeated three times and the mean value will be recorded [35].

Abovementioned outcome measurements will be repeatedly assessed at Week 0 and Week 4. Detailed time points of each outcome assessment are provided in Table 1.

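### A normality pre-test chooses the test and summary for the ordered swallowing scales, so the primary comparison of the Penetration-Aspiration Scale is not fixed in advance

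*Protocol article*

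**What the plan says.** Section 2.12 (Statistical Analysis) sets a two-step rule. First: "One sample of the Kolmogorov-Smirnov test will be used to test the normal distribution of continuous variables". Then the summary follows from the result: "Continuous variables will be shown as means± Standard deviations (SDs) if they are normally distributed or as medians with IQRs" otherwise. So does the between-group test. "If the measurement data have normal distribution, independent two-sample" t-tests compare the groups; "If the measurement data are not normally distributed, the Mann–Whitney" U test does so instead. Within groups the same switch runs between the paired t-test and the Wilcoxon signed-rank test. The section adds: "All statistical tests will be two-sided, and p<0.05 is considered statistically significant".

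The primary outcome has no rule of its own. Section 2.8.1 says "PAS is an 8-point scale to quantify penetration and aspiration severity" and describes its levels as ordered clinical states: 1 no penetration, 2 to 5 penetration, 6 and 7 aspiration, 8 silent aspiration. Section 2.8.2 says "Saitoh's classification divides the swallowing function into 7 levels". Section 2.11 gives the size: "A sample size of 30 per group was regarded as a reasonable minimum recommendation for a pilot study".

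**The concern.** The pre-test asks of PAS and Saitoh a question whose answer is known beforehand: a score confined to 8 or 7 ordered levels is not normal. Passing the check shows only that the sample was too small, or the test too lax, to detect this.

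The check nevertheless decides what the trial reports. One branch gives a comparison of means and the other a rank comparison with medians. A mean difference counts a step from level 3 to 4, both penetration, the same as the step from 7 to 8, into silent aspiration. A rank comparison uses only the order. Which of the two a reader gets depends on the Week 4 distribution, which treatment itself can shift, and the choice may differ between PAS and Saitoh.

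Section 2.11 says that no earlier study of acupuncture on PAS with FEES was found. A summary chosen in advance is therefore one of the more useful things this pilot can hand to a later trial.

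**Working it through.** **Inputs from the protocol article.** PAS levels 1 to 8 (2.8.1); 30 per group, 60 in total (2.11); two-sided 0.05 and the switch rule (2.12). The total is 2 × 30 = 60 from a pilot rule of thumb, so there is no power figure to reproduce. The article gives no PAS distribution, so the shapes below are assumptions, shown as a range.

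**Step 1: critical values at 5%.** The uncorrected Kolmogorov-Smirnov (KS) limit is 1.358/√n: 1.358/√30 = 0.248 and 1.358/√60 = 0.175. The Lilliefors limit, which allows for an estimated mean and SD, is 0.159 at n = 30 and 0.114 at n = 60 (simulated). The article does not say which applies.

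**Step 2: how far an 8-level score lies from its fitted normal.** Example with level shares 0.40, 0.18, 0.12, 0.09, 0.07, 0.05, 0.05, 0.04. The mean is 2.80 and the SD is √(12.20 − 2.80²) = 2.09. The share at or below level 2 is 0.40 + 0.18 = 0.58; the fitted normal gives Φ((2 − 2.80)/2.09) = 0.351; the gap is 0.229. That is below 0.248 but above 0.159, so in a typical sample the unstated variant decides the result.

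| Assumed shape | Largest gap | Rejected, n = 30, uncorrected | Rejected, n = 30, Lilliefors | Rejected, pooled n = 60, uncorrected |
|---|---|---|---|---|
| Uniform | 0.119 | 0.9% | 55% | 11.6% |
| Moderate skew (0.22, 0.20, 0.16, 0.13, 0.10, 0.08, 0.06, 0.05) | 0.172 | 8.4% | 82% | 61.3% |
| Bimodal (0.25, 0.15, 0.06, 0.04, 0.05, 0.08, 0.12, 0.25) | 0.206 | 25.5% | 99% | 95.8% |
| 40% at level 1 (as above) | 0.229 | 47.0% | 99% | 98.3% |
| 60% at level 1 (0.60, 0.13, 0.08, 0.06, 0.05, 0.03, 0.03, 0.02) | 0.335 | 95.9% | 100% | 100% |

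The rejection rates come from 4,000 simulated samples per shape. A separate run gave 0.3% (flat) to 97% (60% at level 1) uncorrected, and 56% to 100% with Lilliefors.

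**Step 3: the whole procedure.** Assume 30 per arm, the uncorrected check in each arm, the t-test if both arms pass and Mann-Whitney otherwise. With no treatment effect, type I error is 4.8% to 5.4%, against 4.7% to 5.2% for Mann-Whitney alone. With an effect:

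| Assumed contrast | Both arms pass | Only one passes | Power, switch | Power, Mann-Whitney | t-test and Mann-Whitney disagree at 0.05 |
|---|---|---|---|---|---|
| Moderate skew vs 40% at floor | 49.1% | 47.1% | 26.2% | 26.7% | 8.4% |
| Uniform vs moderate skew | 91.6% | 8.3% | 45.4% | 44.2% | 4.1% |
| 40% at ceiling vs uniform | 53.4% | 46.2% | 83.3% | 84.0% | 4.0% |
| 40% vs 60% at floor | 1.9% | 52.7% | 32.2% | 32.2% | 11.4% |

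The largest power difference is 45.4 − 44.2 = 1.2 percentage points. Section 2.12 does not say which branch applies when only one arm passes, which happens in 8% to 53% of these runs.

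**Step 4: what a fixed, baseline-adjusted analysis offers.** PAS and Saitoh are already measured at Week 0. If baseline correlates ρ with Week 4, adjustment multiplies the standardised effect by about 1/√(1 − ρ²). Unadjusted power of 58% corresponds to 1.96 + 0.20 = 2.16 standard errors. At ρ = 0.5 this becomes 2.16/√0.75 = 2.50, and power Φ(2.50 − 1.96) is about 70%. Simulation of assumed data starting from 57% to 59% gave 60%, 68% and 82% at ρ = 0.3, 0.5 and 0.7. The correlations are assumptions.

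**The case against.** The strongest reply is textual. Section 2.12 speaks of continuous variables and measurement data and never names PAS or Saitoh, so their passage through the gate is a reading. If the article simply leaves ordinal outcomes to a fuller plan, that is no fault in a condensed article. The first half stands, and the point is worded as an inference. The second does not answer it: the section states a positive rule, names no other between-group test and makes no exception for the primary outcome. A later plan would have to inherit the switch or depart from it.

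The second reply is that the harm is modest. Both branches are named in advance, the statisticians are blinded, type I error holds, and the trial is a 60-person pilot. All of this stands. Blinding limits deliberate selection of a test, but the effect summary still depends on the data.

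Three stronger readings are tempting and are not supported. A reader might infer that the check almost always passes ordinal data. That is so only for the uncorrected test by arm with spread-out scores (0.9% to 8.4% for the uniform, bell-shaped and moderately skewed shapes); with many scores at one end, or with the Lilliefors correction, it often or nearly always fails. A reader might infer a raised false-positive rate, or power lost by switching; Step 3 shows neither.

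**Conclusion.** The point holds as a badly fixed rule. The choice between a t-test with means and a Mann-Whitney test with medians for the primary outcome is left to a normality check that is meaningless for ordered levels. Its result ranges from rejection in under 1% to about 97% of samples (uncorrected, n = 30), or about 55% to 100% (Lilliefors). The KS variant, testing by arm or pooled, and the handling of a split result are not stated.

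The consequence is an unfixed primary test and effect summary. Under the assumed effects the two candidate tests disagree at 0.05 in 4% to 11% of trials, and in 0.7% to 3.4% when there is no effect. The conclusion rests on the inference that section 2.12 governs PAS and Saitoh; the sizes rest on assumed PAS distributions. The correction is worth making, but the point does not put the trial's error rate in doubt.

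**What to change.** In section 2.12, remove the normality gate for PAS and Saitoh's classification. Prespecify one ordinal or rank-based comparison at Week 4, adjusted for the baseline score: for example a proportional-odds model, or rank ANCOVA if levels are sparse. Report an effect estimate that matches the method, its 95% confidence interval, and the count at each level by group. Keep the Mann-Whitney test as a sensitivity analysis. For SWAL-QOL, MMASA and sEMG, use baseline-adjusted ANCOVA without a normality gate.

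The cost is analysis wording only: no added visit, measurement or participant, since baseline scores are already collected. The one drawback is the proportional-odds assumption, which 30 per group can test only weakly; the rank-based sensitivity analysis covers this.

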**Methods and Design:**

Sixty eligible participants will be recruited and randomly assigned into treatment group (He's* Santong* needling method and swallowing rehabilitation training) and control group (swallowing rehabilitation training) in a 1:1 ratio. All treatments will be provided everyday on weekdays with a two-day interval at the weekend, during a total treatment course of four weeks. The Penetration-Aspiration Scale with Fiberoptic Endoscopic Examination of Swallowing will be assessed at baseline and endpoint (Week 4) as primary outcomes. The Saitoh's classification score, Swallowing-Related Quality of Life score, the Modified Mann Assessment of Swallowing Ability score, and Surface Electromyography will be evaluated at baseline and endpoint as secondary outcomes.

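### Section 2.12 fixes a between-group test without baseline adjustment for PAS and every secondary outcome, and does not say whether the Week 4 value or the change is compared; adjusting for baseline would cost nothing and be more precise on either reading

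*Protocol article*

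**What the plan says.** Section 2.12 chooses between two pairs of tests after a normality check. For normal data, an independent two-sample t-test compares the groups and a paired t-test is used within each group ("tests will be used for comparisons among the groups, while paired"). For non-normal data, the Mann-Whitney U "test will be used for comparisons among the groups, while Wilcoxon signed-ranks test will be used for within-group comparisons". The significance rule is "All statistical tests will be two-sided, and p<0.05 is considered statistically significant". No covariate, regression model or other baseline-adjusted comparison appears in the article.

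Baseline values will exist for every outcome. The abstract says of the primary outcome: "The Penetration-Aspiration Scale with Fiberoptic Endoscopic Examination of Swallowing will be assessed at baseline and endpoint (Week 4) as primary outcomes". Section 2.8.2 says of all five outcomes: "Abovementioned outcome measurements will be repeatedly assessed at Week 0 and Week 4", and Table 1 agrees. Section 2.8.1 describes the scale: "PAS is an 8-point scale to quantify penetration and aspiration severity".

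Section 2.11 sets the size without a power calculation: "A sample size of 30 per group was regarded as a reasonable minimum recommendation for a pilot study". Section 2.5 describes 1:1 allocation in blocks of four and states no stratification.

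No passage says whether the between-group test is applied to Week 4 values or to change from Week 0.

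**The concern.** A patient's own baseline score usually predicts the Week 4 score. The trial pays for that measurement on every outcome, including an endoscopy for PAS, but the planned between-group comparison does not adjust for it. The within-group paired tests do use it, but they do not estimate a treatment effect.

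Two things are at stake. The first is precision: with 60 participants fixed by a rule of thumb, the plan gives up precision that the collected data could supply. The second is chance imbalance: blocks of four balance the numbers per arm, not baseline severity, so a baseline difference in PAS can arise and feed into the comparison. Because the text leaves open Week 4 value or change, the direction of that effect is open too. The two choices err in opposite directions, so one of them could be picked after an imbalance has been seen.

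**Working it through.** **The plan's own figure.** 2 x 30 = 60 is consistent. No effect size, SD or power stands behind it, so there is no power calculation to reproduce.

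**Inputs.** From the document: 30 per arm, two-sided 0.05, an 8-level primary scale, measurement at Week 0 and Week 4. Assumed: equal SD at both times (set to 1), and a correlation r of 0.3, 0.5 or 0.7, with 0.2 added in the simulation. The document gives no r.

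**Step 1: relative variance of the group contrast.** Week 4 values: 1. Change: 2(1 - r). ANCOVA on baseline: 1 - r².

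| r | Week 4 | Change | ANCOVA | Unadjusted Week 4 N worth 60 adjusted, 60/(1 - r²) |
|---|---|---|---|---|
| 0.3 | 1 | 1.40 | 0.91 | 66 |
| 0.5 | 1 | 1.00 | 0.75 | 80 |
| 0.7 | 1 | 0.60 | 0.51 | 118 |

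The ratio of change to ANCOVA is 2(1 - r)/(1 - r²) = 2/(1 + r), which is 1.54, 1.33 and 1.18. It never falls below 1, so ANCOVA is at least as precise as either reading of the plan.

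**Step 2: detectable effect (normal approximation).** An unadjusted Week 4 test has 80% power at (1.96 + 0.84) x sqrt(2/30) = 0.72 SD. Multiplying by sqrt(1 - r²), ANCOVA detects 0.69, 0.63 and 0.52 SD. At a true effect of 0.72 SD its power is 84%, 90% and 97.5%; a test on change has 66%, 80% and 95%.

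**Step 3: simulation on an 8-level scale.** Latent normal values were cut into eight levels, equally likely at baseline (an assumption), with 30 per arm, a latent effect of 0.6 SD and 3000 runs per setting. The Monte Carlo standard error is at most sqrt(0.25/3000) = 0.9 points.

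| r | Mann-Whitney, Week 4 | Mann-Whitney, change | Rank ANCOVA | Gain over Week 4 | Gain over change |
|---|---|---|---|---|---|
| 0.2 | 60% | 39% | 61% | 1 | 22 |
| 0.3 | 59% | 41% | 63% | 4 | 22 |
| 0.5 | 58% | 53% | 70% | 12 | 17 |
| 0.7 | 59% | 73% | 82% | 23 | 9 |

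With no true effect, all three methods reject in about 5% of runs.

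**Step 4: chance imbalance.** The SD of the difference in baseline means is sqrt(2/30) = 0.258 SD. P(|difference| > 0.25 SD) = P(|Z| > 0.97) = 33%. P(|difference| > 0.5 SD) = P(|Z| > 1.94) = 5%.

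Given an imbalance D, the estimate shifts by rD for Week 4 values and by (r - 1)D for change. At r = 0.5 and D = 0.5 SD that is +0.25 SD or -0.25 SD, and the type I error given that imbalance is 12.6%. Over r = 0.3 to 0.7 at D = 0.5 SD it is 7.8% to 19.9% for Week 4 values and 15.6% to 9.6% for change. At D = 0.25 SD it stays between 3.6% and 4.9% on both readings.

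**The case against.** The strongest case on the other side has four parts.

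- **The test is valid.** A reader might infer that an unadjusted comparison is biased or inflates false positives. The document does not support that: under randomisation the overall type I error is about 5% on either reading. The bias exists only given an imbalance that has occurred. The 33% figure does not mean that a third of such trials would mislead, since an imbalance of 0.25 SD leaves the conditional type I error at or below 5%. This stands, and it limits the point to efficiency and robustness.
- **Baseline may be used after all.** A reader might infer that the planned tests cannot use baseline. They can: a t-test or Mann-Whitney test on change does so in part, and section 2.12 does not rule that out. So the accurate statement is that neither test adjusts for baseline. The conclusion survives, because change is never more precise than ANCOVA and is worse than the Week 4 value when r is below 0.5.
- **The gain may be small.** Entry is limited to Kubota levels 3 to 5 and to two weeks to three months after onset (section 2.4.1), and the Background says that most patients recover spontaneously. Both could lower r. At r = 0.2 to 0.3 the gain over a Week 4 test is only 1 to 4 points. This stands, so low values of r belong in the range.
- **It is a pilot with no power target.** No stated power claim is broken, and unadjusted tests contradict nothing in the text. True, but the stated aim is to evaluate the effect, with tests at 0.05, and a more precise estimate also serves a later trial.

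The analysis plan is not shown. That does not answer the point, because the article itself names the tests.

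**Conclusion.** The point holds as a should-fix improvement, not as a defect that invalidates the trial. Section 2.12 fixes an unadjusted comparison for outcomes that all have a baseline value, and leaves Week 4 value or change undecided. On either reading a baseline-adjusted comparison is at least as precise.

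The size rests on the assumed r and, for the power figures, on a 0.6 SD latent effect and evenly spread baseline PAS levels. The gain over a Week 4 test is negligible to small at r = 0.3 or below and substantial at 0.5 to 0.7. If change is what the plan means, the gain is smallest at high r (about 9 points at r = 0.7) and larger below that. Exposure to chance imbalance matters mainly for differences near 0.5 SD or more, which about 5% of trials of this size would show if randomisation is unstratified, as the article's silence suggests.

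**What to change.** - **Primary:** state that Week 4 PAS is the outcome, and compare groups with a proportional-odds model or rank ANCOVA with baseline PAS as covariate. Report an effect estimate with 95% CI where the model gives one; the proportional-odds model does so directly.
- **Saitoh's classification (7 levels):** use the same ordinal or rank form with its own baseline.
- **SWAL-QOL, MMASA and sEMG:** use linear ANCOVA on the Week 4 value with its own baseline.
- **Supporting:** keep the t-test or Mann-Whitney U test, and say which quantity it is applied to.

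Naming Week 4 as the outcome is needed in its own right. In linear ANCOVA, adjusted change and adjusted Week 4 value give the same treatment effect, but that identity does not carry over to the proportional-odds model or rank ANCOVA.

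The cost is a few lines of text, settled before the outcome data are unblinded. No new data, visits or participants are needed.
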